### Data Analysis

#### Sociodemographic and Clinical Data

Sociodemographic and clinical data will be presented as percentages, means, and standard deviations or medians and interquartile ranges depending on the distribution of the data.

#### Medication Adherence

All dates and the timing of electronic monitor activation will be used to analyze medication adherence. Electronic monitor data will be reconciled with pill counts and patient reports [26]. The global adherence will be calculated as the percentage of days during which the drug is taken properly across the individual study duration. Two-sided Student *t* test will be used to compare the mean probabilities between groups in the logit scale. A difference between groups will be considered statistically significant if *P*<.05. Medication behaviors are characterized by implementation, persistence, and longitudinal adherence [27].

Implementation evaluates at each day the proportion of patients taking at least the correct dose prescribed on that day among the patients who are still participating in the program. For each participant, the daily medication behaviors will be described with a binary variable (1=at least the correct number of daily openings of the electronic monitor for all drugs monitored; 0=fewer daily openings than prescribed for at least one drug monitored). This code is commonly used and cannot discriminate overadherence, which will be considered as adherence. Implementation will be modeled with the generalized estimating equation multimodeling [28].

Persistence corresponds to the distribution of times between inclusion in the study and discontinuation (ie, unilateral stopping of treatment by the patient). Persistence will be described with a Kaplan-Meier survival curve. The log rank test will be used to compare the persistence between groups [28].

Longitudinal adherence is defined at each day as the proportion of patients taking at least the correct dose prescribed on that day among all the patients included in the study. Longitudinal adherence will be presented as the product of persistence and implementation and modelized by generalized estimating equation multimodeling [28]. In an exploratory analysis, univariable and multivariable regressions will analyze the associations among medication behaviors (combining persistence and implementation), sociodemographic and clinical data at inclusion, and changes in the clinical and biochemical variables at the completion of the study.

The number of patients with adherence rates less than 30% in the postintervention monitoring phase for at least one drug during 2 consecutive pharmacy visits will be compared between groups with a chi-squared test or with Fisher exact test if the sample size is less than 5 patients. The statistician who will perform the analysis will not be aware of the group allocation until the data are completely frozen. Statistical analysis will be performed with the R statistical package (version 3.6, The R Foundation for Statistical Computing) [29].

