### Randomized Controlled Medication Adherence Study

The inclusion and exclusion criteria are presented in Textbox 1 and Textbox 2, respectively.

Inclusion criteria for the participants.Adults older than 18 years who are being followed in the University Hospital and have type 2, type 1, latent autoimmune diabetes in adults, or corticoid-induced diabetesOne of the following biochemical criteria: estimated glomerular filtration rate (eGFR)≤60 mL/min/1.73 sq m, eGFR>60 mL/min/1.73 sq m that has deceased >5 mL/min/year, urine albumin/creatinine ratio >30 mg/mmol, patients hospitalized at least twice for acute renal impairment in the past 5 years.Treatment with at least one of the following drug classes: oral antidiabetic drugs (metformin, dipeptidyl peptidase-IV inhibitors, sodium-glucose cotransporter-2 inhibitors, sulfonylureas, glinides), statins, diuretics, beta-blockers, calcium antagonists, alpha-blockers, angiotensin-converting-enzyme inhibitors, angiotensin II receptor blockers, or aspirin.Fluency in French or English. If not, the presence of an interpreter at each medication adherence visit.Full blood test (eGFR, glycated hemoglobin, albumin/creatinine ratio or total, high density lipoprotein and low-density lipoprotein cholesterol) in the 6 months prior to inclusion.

Exclusion criteria for the participants.Incapacity to make decisions, having cognitive disorders, or being under tutelagePregnancyActive cancer (not in the remission phase)Treatment of the patient is managed by nursing homes or home care servicesPatients already included in an intervention study

All the pharmacists providing the IMAP intervention were trained in motivational interviewing at the University community pharmacy of Unisanté [12]. The technicians were trained in how to complete the electronic monitor data, count pills, and use the MedAmigo software (MEMS and MEMS AS, Aardex Group) to upload electronic monitor adherence data and generate a medication adherence report.

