### Intervention

#### Use of the Electronic Monitor

In both groups, patients use electronic monitors for 24 months. Electronic monitors register the date and hour of each opening, which corresponds to the moment of the drug intake as long as both behaviors are consecutive. Nevertheless, one limitation of this tool is that patients could open the electronic monitor without taking the drug or swallowing it long after the electronic monitor opening. In order to limit this bias and before showing the electronic monitor data to the patient at each pharmacy visit, pharmacists check with the patients that each opening corresponds to the drug intake. They ask the patient about the usual lapse of time between each opening and the real time of the drug intake. The liquid-crystal display (LCD) screen on top of the electronic monitor cap resets at 3 AM each morning. Hence, each time the patient opens the electronic monitor cap, the LCD shows the number of cumulative openings until 3 AM on the next day. The LCD screen reminds the patient about whether the medication has been taken or not.

Drugs to monitor are prioritized based on the following algorithm, which we constructed based on side-effect profiles: (1) all oral antidiabetic drugs, (2) statins, (3) diuretics, (4) beta-blockers, (5) calcium antagonists, (6) alpha-blockers, (7) angiotensin-converting-enzyme inhibitors, (8) angiotensin II receptor blockers, and (9) aspirin. Moreover, in each class, eligible drugs taken more than once a day prioritize monitoring. The maximum number of monitored drugs is 6. Physicians can modify the treatments at any time. If a patient has to stop all the monitored drugs, he or she will stop the study but the data collected until then will be kept for analysis. If a drug is switched to another eligible drug, the new prescribed drug will be monitored.

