### Postintervention Monitoring Phase

After the intervention phase, patients will still use electronic monitors with their LCD screens, but their adherence data will be double-blinded. Patients will not receive any feedback or motivational interviews about their daily drug management. The clinical team will not obtain any adherence reports. Due to ethical reasons, if the medication adherence rate detected by the MedAmigo software is less than 30% for at least one drug for 2 consecutive pharmacy visits, the software will automatically notify the pharmacist, and the patient will stop the study and will be oriented to the routine IMAP. If a physician in charge of a patient explicitly asks to access the adherence data during the postintervention monitoring phase for clinically urgent and important reasons, the principal investigator will sign a permission form that will be included in the case report form, and the patient will stop the study. All the data collected until then will be kept for analysis. At 18 months after the inclusion, during the postintervention monitoring phase, blood and urine samples will be collected to determine the clinical values at this time point. Indeed, the frequency of blood and urine samples collection differs between patients, and collecting laboratory values for each patient at this precise time point will ensure consistency in the analysis.

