#### Sample Size

An expert committee composed of nephrologists, endocrinologists, nurses, pharmacists, and statisticians agreed that the difference in the mean global adherence between groups should be 5%. The hypothesis states that the adherence rate will average 97.5% in the 12-month intervention group and 92.5% in the 6-month intervention group. A standard deviation of 1.7 was assumed in the logit scale in both groups. This corresponds to 95% global adherence in the intervals (57.5%-99.9%) and (30.0%-99.7%) for the 12-month intervention group and the 6-month intervention group, respectively. According to these parameters, a sample size calculation was made simulating individual series of daily medication (1=at least the correct number of daily openings of the electronic monitor for all drugs monitored; 0=fewer daily openings than prescribed for at least one drug monitored), in order to consider both the interindividual variability (SD 1.7) and the intraindividual variability (the measurement error). Considering that the mean number of measures of a subject will be 365, 72 patients must be included in this study (36 participants in each group) to have a power of 80% and a two-tailed alpha error of .05. Regarding the qualitative study, the expert committee agreed that a subgroup of 14 included patients will attend the qualitative interview but more patients may be included if data saturation is not reached after the completion of 14 interviews.

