### Limitations

This study has some limitations. First, patients are included for 24 months in this study, which is a relatively long period of time, thereby increasing the probability of change in regimen over time and dropouts. In addition, the adherence data analysis is complex as patients use more than 1 electronic monitor. However, complex medication adherence data analysis was previously developed by the investigators, and the statistician who will perform the analysis is an expert in this field. Secondly, we cannot exclude the Hawthorne effect during the first 6 weeks of this study, explained by the fact that participants might improve their usual medication adherence behaviors as they feel observed [30]. We will analyze adherence as a trajectory (longitudinal, repeated measures) and we will pay attention to this risk during our analysis. All limitations and their possible impacts on the results will be clearly depicted in the final publication.

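### The all-drugs daily code ties the primary outcome to the number of monitored drugs, but the primary t test does not use that number: some precision is lost, and regimen changes can move the score

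*Protocol article*

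**What the plan says.** Under Medication Adherence, each patient-day is coded 1 only if every monitored drug had enough openings; the other value is defined as "0=fewer daily openings than prescribed for at least one drug monitored". The sentence stands in the paragraph on implementation. The Sample Size section uses the same code for the comparison of global adherence, where "a sample size calculation was made simulating individual series of daily medication". The definition of the primary outcome is less explicit, because it speaks of a single drug: "The global adherence will be calculated as the percentage of days during which the drug is taken properly across the individual study duration".

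The number of monitored drugs is not fixed. Eligibility requires "Treatment with at least one of the following drug classes", so one drug is enough. Under Use of the Electronic Monitor: "The maximum number of monitored drugs is 6. Physicians can modify the treatments at any time".

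For the primary comparison, a two-sided Student t "test will be used to compare the mean probabilities between groups in the logit scale". No covariate is named. Randomisation (Assignment of Interventions) is 1:1 within four strata formed by statin use and by any drug taken more than once daily; the number of drugs is not a stratum. Monitored treatments are listed as covariables only for the ADVANCE and UKPDS models. The Limitations section says of the 24-month duration "thereby increasing the probability of change in regimen over time and dropouts" and notes that several monitors make the analysis complex.

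**The concern.** Two patients who handle each drug equally well can receive different scores because one has more monitors. This has two consequences, which need to be kept apart.

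- **Between patients.** The drug count at inclusion adds spread to the primary outcome. The trial already holds this number, and a covariate could remove the spread. What is at stake is power.
- **Within patients over time.** If a monitor is added or removed, the score can move with no change in behaviour. This affects the reading of the trajectories at 6, 12, 18 and 24 months and, through the average over follow-up, the global score. A covariate measured at inclusion does not deal with it.

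**Working it through.** **Inputs from the article (Sample Size).** Means 97.5% and 92.5%; SD 1.7 on the logit scale in both groups; 365 measures per patient; two-sided alpha 0.05; power 80%; 36 per arm.

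**Inputs assumed, because the article does not give them.** Each drug is taken correctly on 98% of days. A share r of each drug's misses are whole-day misses that hit all drugs together; the rest are independent. Drug counts are uniform either on 1 to 6 or on 3 to 6.

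**Step 1: the plan's own figure.** logit(0.975) − logit(0.925) = 3.664 − 2.512 = 1.151. The standard error at 36 per arm is 1.7 × √(2/36) = 0.401, so the noncentrality is 1.151/0.401 = 2.87. With 70 degrees of freedom, power is 80.9%. Simulating 365 binary days per patient gives 78.5% at 36 per arm and 80.2% at 37. The stated sample size is reproduced.

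**Step 2: how the score depends on the count.** Let s = 0.02r be the probability of a shared miss. The probability that all k drugs are correct on a day is (1 − s) × [0.98/(1 − s)]^k.

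| Misses shared (r) | k = 1 | k = 3 | k = 6 | Spread, 1 to 6 |
|---|---|---|---|---|
| 0 (independent) | 98.0% | 94.1% | 88.6% | 9.4 points |
| 50% | 98.0% | 96.0% | 93.1% | 4.9 points |
| 80% | 98.0% | 97.2% | 96.0% | 2.0 points |
| 100% | 98.0% | 98.0% | 98.0% | 0 |

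The score never rises with k, and it is flat when all drugs are missed together. The design difference is 5 points.

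**Step 3: precision.** Take the variance V of these logits over the assumed counts and suppose that SD 1.7 already contains it. The residual SD after adjustment is √(1.7² − V) = √(2.89 − V).

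| Counts | r | V | V/2.89 | Residual SD | Power at 36 per arm |
|---|---|---|---|---|---|
| no adjustment | – | – | – | 1.700 | 80.9% |
| 3-6 | 80% | 0.018 | 0.6% | 1.695 | 81.1% |
| 3-6 | 50% | 0.046 | 1.6% | 1.686 | 81.5% |
| 3-6 | 0 | 0.073 | 2.5% | 1.678 | 81.9% |
| 1-6 | 80% | 0.058 | 2.0% | 1.683 | 81.7% |
| 1-6 | 50% | 0.189 | 6.5% | 1.643 | 83.4% |
| 1-6 | 0 | 0.387 | 13.4% | 1.582 | 86.1% |

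These powers assume that the covariate captures all of the count-related spread, so each is an upper limit for its row.

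**Step 4: validity.** Counts were simulated at random from 1 to 6 in both arms, with independent misses and no change related to arm. The unadjusted t test then had a type I error of 5.1%, so it keeps its size.

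**Step 5: change within a patient.** Going from 3 to 4 monitored drugs moves the score from 94.1% to 92.2% with independent misses, and from 97.2% to 96.8% with 80% shared. With all misses shared it does not move.

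**The case against.** The strongest reply is that the planned test is valid. Randomisation balances the count at inclusion in expectation, and leaving out a prognostic covariate is a choice about efficiency. That stands. A reader might infer from the 9.4-point spread that the primary comparison is biased. The documents do not support this: the spread lies between patients with different counts, not between arms.

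Second, the SD of 1.7 was assumed for this same all-drugs series, so it plausibly already contains the count spread and the design loses nothing. This is the natural reading, and the table in the working follows it. On the other reading, with 1.7 excluding that spread, unadjusted power would fall to 75.8% in the extreme case (SD √(2.89 + 0.387) = 1.81).

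Third, the large gains need both independent misses and counts uniform on 1 to 6. The Introduction says that these patients often take more than five daily treatments, which makes many single-drug patients doubtful, although not every treatment need be eligible for monitoring. With counts of 3 to 6 the gain is one power point or less.

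Fourth, a reader might infer that drug counts drift apart by arm after month 6. Adherence reports go to the clinical team during the intervention, and afterwards "The clinical team will not obtain any adherence reports", so prescribers hold reports for 12 months in one arm and 6 in the other. The route is possible. Yet the document gives no counts by arm and does not say that reports change the number of drugs; a one-for-one switch leaves the count unchanged, and the count is capped. Prescribing changes that follow from the reports could also belong to the effect of a longer programme. If mean counts of 3 versus 3.5, or 3 versus 4, were assumed with independent misses, type I error would be 6.5% or 10.4%. These figures illustrate a hypothetical and are not a finding.

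Fifth, the strata cover part of regimen complexity, and exploratory multivariable regressions are planned. Neither changes the named primary test, which is a stated choice.

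**Conclusion.** The point holds as a matter of precision and interpretation. The code can only stay equal or fall as monitored drugs are added, and the stated primary test ignores a count known at inclusion. On the assumptions above, adjustment lifts power from 80.9% to about 81-82% for counts of 3 to 6, and to about 82-86% for counts uniform on 1 to 6. If all misses are shared, the gain is nil. The t test remains valid without adjustment.

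A change of regimen during follow-up can move the score without a change in behaviour, by about 2 points per added drug at most under these assumptions. Whether this differs by arm cannot be known from the document. The change is worth making because it is cheap, not because the planned result would be wrong without it.

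**What to change.** In Medication Adherence:

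1. State that global adherence uses the all-drugs daily code, since the present definition refers to one drug only.
2. Replace the t test by a linear model on the same logit-scale outcome, with arm and the number of monitored drugs at inclusion, ideally together with the randomisation strata. Do not adjust for the count after randomisation, which the intervention may itself affect.
3. Add a supportive analysis that scores each monitored drug separately and averages per patient. Repeat it for drugs monitored from inclusion only. This is the part that addresses regimen change.
4. Report the mean number of monitored drugs by arm at 6, 12, 18 and 24 months.

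The cost is a few degrees of freedom, one supportive analysis and one extra table. No new data should be needed, because the rule on adherence below 30% for at least one drug already requires a rate for each drug. The change should be fixed before the data are frozen and the analysing statistician learns the allocation.

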### Assignment of Interventions

Patients are randomized 1:1 at inclusion to either the 12-month or 6-month intervention group. According to the risk of nonadherence due to the adverse effects of statins or the complexity of the drug regimen, 4 randomization groups were created: patients treated with statins, patients who have to take at least one drug more than once daily, patients with both of the former conditions, and patients with none of the former conditions. Then, the randomization is performed in each strata and is coded with 0, corresponding to group A, where patients receive the intervention for 12 months, or 1, corresponding to group B, where patients receive the intervention for 6 months. The randomization code is generated by a random repetition of 4 and 6 blocks composed of 1 or 0 (Excel, Microsoft) to prevent predictability of the sequence. The randomization sheets were created by an independent researcher from the Unisanté Research Support Unit. The allocation is established for each consecutive patient by unsealing the randomization sheet. This study is open, and the clinical team as well as the patients are aware of the allocation group.

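### Randomisation is stratified on two nonadherence risk factors, but the t test for global adherence cannot use them; if they predict adherence, some precision is given up

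*Protocol article*

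**What the plan says.** **Allocation.** Under Assignment of Interventions, four strata are formed: statin treatment, at least one drug taken more than once a day, both, or neither. The reason given is the risk of nonadherence, from statin side effects or from regimen complexity. Allocation is blocked (sizes 4 and 6) inside each stratum: "Then, the randomization is performed in each strata and is coded with 0, corresponding to group A".

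**Analysis of global adherence.** The Medication Adherence section names a two-sided Student t test, which "will be used to compare the mean probabilities between groups in the logit scale". No covariate is attached to it.

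**Analysis of persistence.** "The log rank test will be used to compare the persistence between groups". The article does not say whether this test is stratified.

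**Sample size.** It rests on the same comparison: "the adherence rate will average 97.5% in the 12-month intervention group and 92.5% in the 6-month intervention group". The spread between patients is set in the same section, with one value for the two arms: "A standard deviation of 1.7 was assumed in the logit scale in both groups". The result is 36 per group "to have a power of 80% and a two-tailed alpha error of .05".

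Covariates appear only in the exploratory regressions and in the models for the ADVANCE and UKPDS scores. Neither is the main comparison, and neither names the strata.

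**The concern.** Blocking within strata makes the arms nearly equal on the two factors. Whatever variance those factors explain then contributes almost nothing to the actual sampling error of the difference between arms. A two-sample t test does not know this. It leaves that variance in its error term and reports a standard error larger than the true one.

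There is reason to expect at least a modest effect. The sponsor chose the factors for nonadherence risk. The daily outcome also counts as adherent only if every monitored drug has at least its prescribed number of openings, so a drug taken twice daily gives more ways to fail.

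At stake is efficiency. The Results section reports 73 enrolled and recruitment closed, and dropouts are not replaced, so the number of patients cannot grow. How the strata are handled in the analysis is still open to change.

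**Working it through.** **1. Inputs from the Sample Size section.** Means 97.5% and 92.5%, SD 1.7 on the logit scale, 36 per arm, two-sided 5%.

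- logit(0.975) = ln(0.975/0.025) = 3.664
- logit(0.925) = ln(0.925/0.075) = 2.512
- Difference δ = 1.151; δ/SD = 1.151/1.7 = 0.677
- SE of the difference = 1.7 × √(2/36) = 0.401; δ/SE = 2.873

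**2. The plan's own figure.** The noncentral t with 70 degrees of freedom and noncentrality 2.873 gives 80.9% power at 36 per arm, and 36 is the smallest number that reaches 80%. The stated 72 is reproduced. A simulation that also draws 365 binary days per patient gives 78.6%, still close to 80%. The SD of 1.7 is the total SD, with no credit taken for the strata.

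**3. Assumption.** Let R² be the share of the logit-scale variance explained by the strata. The documents give no value, so a range is used. To gauge the scale, suppose each opening succeeds independently with probability 0.97 and half the patients have a twice-daily drug. Correct days are then 97.0% or 0.97² = 94.1%, a logit gap of about 0.71. That factor explains 0.71² × 0.25 / 1.7² = about 4% of the variance, before any statin effect.

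**4. Formulas under stratified blocks.**

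- True SE of the difference = 0.401 × √(1 − R²), while the t test goes on reporting about 0.401.
- True type I error of the t test ≈ 2[1 − Φ(1.96/√(1 − R²))].
- Power of the t test ≈ Φ((2.873 − 1.994)/√(1 − R²)), with 1.994 the critical value at 70 degrees of freedom.
- Power of the model with arm and two binary terms: noncentral t with 72 − 4 = 68 degrees of freedom and noncentrality 2.873/√(1 − R²).

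| R² | True SE | t-test type I error | t-test power | Adjusted power | Gain (points) |
|---|---|---|---|---|---|
| 0 | 0.401 | 5.0% | 81.0% | 80.9% | about 0 |
| 0.05 | 0.391 | 4.4% | 81.6% | 82.8% | 1.2 |
| 0.10 | 0.380 | 3.9% | 82.3% | 84.7% | 2.5 |
| 0.20 | 0.358 | 2.8% | 83.7% | 88.6% | 4.9 |

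(Gains are taken before rounding.)

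**5. Check by simulation.** 72 patients in four strata, permuted blocks of 4 and 6, t test against a linear model with the strata:

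| R² | t-test type I error | Adjusted type I error | t-test power | Adjusted power |
|---|---|---|---|---|
| 0 | 5.0% | 4.9% | 81.6% | 81.5% |
| 0.05 | 4.5% | 4.9% | 81.7% | 82.9% |
| 0.10 | 3.7% | 4.8% | 81.7% | 84.4% |
| 0.20 | 3.2% | 5.0% | 84.0% | 89.1% |

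At R² = 0.10 the t test reported a mean SE of 0.399 against a true SD of 0.379, about 5% too large. The simulated gains (1.2, 2.7 and 5.1 points) agree with the formulas.

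**6. Log-rank test.** This was simulated with an assumed hazard ratio of 0.5 between arms, censoring at 24 months and about 21 to 39 events. The strata hazard ratio compares patients with both factors to patients with neither.

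| Strata hazard ratio | Unstratified power | Stratified power |
|---|---|---|
| 1 | 34.0% | 33.4% |
| 2 | 44.0% | 44.4% |
| 4 | 52.1% | 56.8% |

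Only the strongest strata effect makes a visible difference.

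**The case against.** The strongest reply is that nothing here is invalid. The trial was sized on the total SD, so the planned 80% belongs to the unadjusted test, and that test delivers it. The error from ignoring the strata is in the conservative direction. This stands, and it limits the point to efficiency.

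A second reply is that the size is unknown. A stated reason for choosing the factors is not evidence that they explain variance in adherence to all monitored drugs. This also stands: the loss is conditional on R², and at R² = 0 there is none. But adjustment then costs essentially nothing either, so the uncertainty is no reason to keep the t test.

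Three stronger readings are tempting:

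- **Gains of 2, 4 and 8 points.** A reader might set the adjusted powers against a fixed 80.9%. That is the wrong comparator, because stratified blocks also raise the t test's own power as R² grows.
- **An unstratified log-rank test as a second error.** The article does not say the test is unstratified. An analysis plan may settle this, and the simulated loss is near nil unless the strata act strongly.
- **A fault in the GEE models.** The article neither lists nor excludes covariates for implementation and longitudinal adherence, and such lists commonly sit in the analysis plan.

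The same defence does not cover the t test. It is named outright, and a two-sample t test cannot carry strata.

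**Conclusion.** The point holds as a mismatch between a stratified design and a named test that cannot use the strata. To the extent that statin use and dosing frequency predict adherence, the t test is conservative and gives up about 1, 2.5 and 5 points of power at assumed R² of 0.05, 0.10 and 0.20, with nothing lost at zero. These sizes rest on the plan's own difference and SD, full retention of 36 per arm, and an R² that the documents do not supply. The direction is secure if the strata matter; the size is not known.

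A reader might infer that the trial is underpowered, biased or wrongly sized because of this. The documents do not support that: 72 reproduces, the planned power is kept to within about two points, and the type I error is not inflated by ignoring the strata.

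**What to change.** Replace the t test by a linear model of logit global adherence on arm plus two binary terms: statin treatment (yes/no) and any drug taken more than once daily (yes/no). Test the arm coefficient two-sided at 5%. It estimates the same mean difference on the logit scale. Two main effects use 2 degrees of freedom and avoid problems with sparse strata. Keep the unadjusted t test as a sensitivity analysis.

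Stratifying the log-rank test by the same factors is optional, for consistency. If it is done, state in advance how sparse strata are merged, because events may be few.

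The cost is a change of wording and 2 of about 70 degrees of freedom. The stratum had to be known for each patient at randomisation, so no new data are needed. The article keeps the statistician unaware of allocation until the data are frozen, so the change can be fixed before then without compromising the analysis.
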